#### **Data Management, analysis and reporting:**

All data collected will be cross-checked by the field supervisors at field offices on a daily basis before handing over to data management unit (DMU). The data will be transferred to the Field Data Management Center at District RYK from the field stations. Prior to data entry, all forms will be checked for completeness and consistency as well as coding of open-ended responses and area codes, etc. In case of inconsistency or missing responses, the editors will flag the errors/omissions and consult the interviewers for possible explanations. The data entry interface will be designed to check for referential integrity, missing values and acceptability constraints, and there were further checks for heaping at the database level. Errors identified at any level will be referred back to the field for correction.

For data entry, databases and entry screens will be developed using Microsoft FoxPro. The entry screens will employ range and consistency checks and skips to minimize entry of erroneous data. Special arrangements will be made to enforce referential integrity of the database so that all data tables are related to each other without problem. A sub sample of the data will be manually checked to examine data entry errors and to monitor error rates of data entry operators. The data will be double entered.

#### **Analysis of qualitative data**

Analysis of qualitative data will give more comprehensive and valid picture for implementation of intervention package. The survey will provide numerical data on distribution of characteristics while the FGDs will provide explanatory insights. Data will be analyzed to develop an understanding of socio-economic, behavioral, situational (i.e., interrelationships, family

dynamics), and environmental (e.g., home, community, etc.) factors that influence a women's choice of having a skilled personnel assisted delivery. Following would be the major themes:

- The barriers and enablers of the skilled care service provision and its uptake in the communities, particularly in poor and marginalized population;
- The role of socio-cultural factors influencing women's choice for birth attendant;
- Quality of care at facilities, community perception on quality of care, support and health workers incentives.

While analyzing data, attention will be given to areas where there are agreements as these may result from censoring of information by participants themselves. This data reduction process will facilitate in identifying the important themes within the data in relation to socio-cultural factors that influence a women's choice to have a skilled delivery. The research team members will have a debriefing session after each focus group session to identify issues which could potential affect analysis (e.g., group dynamics), and identify strategies to improve future focus group sessions.

## **2. Statistical analysis of Quantitative Data**

For data analysis SPSS version 19 will be used and data will be analyzed using univariate and multivariate methods. Reports will be generated fortnightly for senior management of project to review the progress of implementation of interventions.

Primary analysis will be undertaken as intention-to-treat at cluster level. All usual residents of a household who have resided in the study area for >15 days in succession during the 6 months prior to delivery, and delivered during the study period will be considered eligible for analysis, regardless of the place of delivery. Analysis will be done at cluster level using SPSS 19.0 (SPSS Inc., Chicago, Illinois, USA). To account for clustering, point estimates for SBRs, NMRs and perinatal mortality rates for each study arm will be calculated as the mean of cluster event rates, giving an equal weight to each cluster. We will undertake both unadjusted and adjusted analysis of outcomes. We will similarly evaluate differences between intervention and control clusters for cause specific NMR although the study is only powered for the primary all cause neonatal mortality outcomes. Ideally, randomization will take care of confounders, but based on the analysis of baseline characteristics, we will adjust other confounders (if any).

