### **Active Surveillance**

We will also conduct active surveillance in the community to obtain vital statistics in the communities of all arms of the study and to evaluate the trends between intervention and control clusters over time. Special data collection teams will be constituted and will work independent of LHWs and other health staff. These data collection teams will collect information from each village on;

- movement of households members and additional population influx
- pregnancies
- live births, stillbirths, neonatal & maternal deaths
- cases of birth asphyxia, sepsis and low birth weight infants,
- Maternal and neonatal referrals etc.

The data will be collected and recorded on standardized forms by a regular system of community visits and also cross-checked by reviewing local hospital records.

At the end we will evaluate the impact of the interventions on the target population. The evaluation will concentrate on impacts of development and implement intervention package for community-level care workers in representative study areas aimed at reducing postpartum maternal and neonatal mortality and morbidity. The results of last surveillance round will be compared with baseline findings, and impact assessment of the interventions will be made on the major domains of evaluation including:

- Design.
- Impact on the primary and secondary outcomes.
- Program efficiency.

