### **Study Outcome & Process Indicators (at the end of each yr (total 3)**

The primary outcome variables will be:

- All cause neonatal mortality rate
- Perinatal mortality rate

Secondary outcomes

- All cause maternal mortality
- Cause specific maternal mortality such as deaths related to postpartum hemorrhage, puerperal sepsis, eclampsia, obstructed labor, unsafe abortion and indirect causes
- Maternal morbidity such as (including obstetric fistula, eclampsia and obstetrical sepsis
- Cause specific neonatal mortality such as deaths related to birth asphyxia, prematurity, and sepsis.

The key process indicators include:

1. Proportion of women attended by CMWs/LHWs for ANC

2. Proportion of women supplemented with iron/folate
3. Proportion of women received TT immunization
4. Proportion of births attended by CMW
5. Proportion of births in which LHW was present
6. Proportion of women delivered at institution
7. Proportion of deliveries attended by TBAs
8. Proportion of clean delivery kits used
9. Proportion of women with high-risk pregnancy received referral
10. Proportion of women stabilized or managed before shifting to referral facilities.
11. Proportion of women received comprehensive EmOC services among those who were referred
12. Proportion of newborns seen by CMWs/LHW around day 1, 3, 7 and 28
13. Proportion of newborns resuscitated by CMWs, LHWs and TBAs respectively
14. Proportion of CMWs/LBW able to manage hypothermia
15. Proportion of neonates breastfed in an hour of birth
16. Proportion of neonates avoided pre lacteal feeds
17. Proportion of neonates delayed bathing for at least 6 hours
18. Proportion of neonates who received emollient application
19. Proportion of community participated in support group

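### The only analysis-eligibility rule requires a delivery, so as written it removes unsafe-abortion deaths and other undelivered deaths from the secondary maternal-mortality outcomes

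*Protocol*

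**What the plan says.** The protocol's section *2. Statistical analysis of Quantitative Data* opens its main paragraph with "Primary analysis will be undertaken as intention-to-treat at cluster level". The next sentence defines who is analysed. Its first condition is a minimum unbroken stay of more than 15 days, looked for in the half-year before the birth. Its second condition reads "and delivered during the study period will be considered eligible for analysis, regardless of the place of delivery". No other analysis population appears anywhere in the protocol.

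The section *Study Outcome & Process Indicators* makes neonatal and perinatal mortality primary. Among the secondary outcomes are "All cause maternal mortality" and, as a separate item, "Cause specific maternal mortality such as deaths related to postpartum hemorrhage, puerperal sepsis, eclampsia, obstructed labor, unsafe abortion and indirect causes".

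The section *Active Surveillance* has independent teams record pregnancies and "live births, stillbirths, neonatal & maternal deaths". It sets no condition that the woman must have delivered.

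**The concern.** The rule suits births: a stillbirth, perinatal death or neonatal death presupposes a delivery. It does not suit deaths of mothers. A woman who dies after an unsafe abortion has not delivered in the ordinary sense of the word. Nor has a woman who dies of eclampsia before the birth, or of obstructed labor with the baby unborn. Such a woman fails the rule twice. She did not deliver in the study period, and she has no delivery date from which to count residence.

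Two things are at stake. First, one named cause-specific outcome would be zero by construction, and all-cause maternal mortality would be under-counted even though surveillance had recorded the deaths. Second, reaching delivery happens after randomisation and lies on the pathway the package is meant to change, through recognition of high-risk pregnancies, stabilisation, transfer and post-abortion care. Conditioning eligibility on it sits badly with the intention-to-treat analysis promised in the sentence before.

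**Working it through.** **1. The texts side by side.**

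| Named cause of maternal death | Must the woman have delivered? | Effect of the rule as written |
|---|---|---|
| Postpartum hemorrhage, puerperal sepsis | Ordinarily yes | Little or none |
| Eclampsia | No | Undelivered deaths dropped; deaths after delivery kept |
| Obstructed labor | No | Undelivered deaths dropped; deaths after delivery kept |
| Unsafe abortion | No delivery occurs | All dropped |
| Indirect causes | No | Undelivered deaths dropped |

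**2. The plan's own figure, to fix the number of births.** Inputs from *Sample Size Calculation*: cluster population 15,000; 20 births per 1,000 per year; 3 years; perinatal mortality 60/1,000, reduced by 25% to 45/1,000; between-cluster coefficient of variation k = 0.125; 10 clusters per arm; 90% power. Two-sided alpha of 0.05 is assumed, because none is stated.

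Births per cluster: m = 15,000 × 0.020 × 3 = 900.

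Hayes–Bennett formula for unmatched clusters:

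c = 1 + (1.96 + 1.2816)² × [(p0(1−p0) + p1(1−p1))/m + k²(p0² + p1²)] / (p0 − p1)²

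- (0.0564 + 0.042975)/900 = 0.0001104
- 0.125² × (0.0036 + 0.002025) = 0.0000879
- c = 1 + 10.507 × 0.0001983 / 0.000225 = 10.26 per arm

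Ten per arm gives power of 0.892. The stated design reproduces, so 900 births per cluster is the right basis.

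**3. Expected maternal deaths, both arms together.** Total births: 20 × 900 = 18,000, treated as live births.

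- District ratio of 103 per 100,000 (*Health Indicators*): 18,000 × 0.00103 = 18.5
- National ratio of 276 per 100,000 (*Maternal and neonatal health in Pakistan*): 18,000 × 0.00276 = 49.7

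**4. Deaths the rule would drop.** The protocol does not give the share of maternal deaths that occur undelivered or after abortion. The shares below are assumptions.

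| Assumed share | Of 18.5 | Of 49.7 |
|---|---|---|
| 5% | 0.9 | 2.5 |
| 10% | 1.9 | 5.0 |
| 20% | 3.7 | 9.9 |
| 30% | 5.6 | 14.9 |

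These are totals across both arms. The nearest figure in the protocol is in *Justification of the Study*: 11–17% of maternal deaths happen during childbirth itself. That is not the undelivered share. Some of those women will have delivered, and abortion and antepartum deaths are additional.

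**The case against.** The strongest reply is that the rule was never meant for maternal outcomes. It directly follows a sentence on the primary analysis, and both primary outcomes presuppose a delivery. The rest of the paragraph speaks only of stillbirth, neonatal and perinatal rates and cause-specific neonatal mortality. On that reading the maternal population is merely unstated, which a protocol may leave to its SAP. This reading is plausible and may be what the authors intended. It does not settle the matter. The rule speaks of eligibility for analysis without limit, the same paragraph goes on to a secondary outcome, and no alternative population is offered. An analyst following the text would drop these deaths.

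Other parts of the reply stand in full. Nothing is lost at data capture. Women with eclampsia or obstructed labor who deliver and then die remain counted, so the conflict is complete only for unsafe abortion. The study is not powered for maternal mortality.

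A reader might infer more: that control-arm women die undelivered more often, so the rule biases against the package, or that losing a few deaths could reverse the comparison. The documents do not support either claim. They give no rate of undelivered death by arm. Facility training and emergency trays go to both arms, and the referral pathway is to be strengthened throughout the study area. The loss falls on both arms, so only the difference between the two losses could distort a comparison. With about 9 deaths per arm at the district ratio (18.5 / 2), chance alone could reverse the comparison under any rule. Nor is there ground for saying that the excluded deaths are the most severe cases, because the outcome is death in every case.

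**Conclusion.** The rule is wrong as written for the maternal-mortality outcomes. It excludes every unsafe-abortion death, although that cause is named, and every other death of an undelivered woman. This follows from the text alone.

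The number lost rests on assumptions: the plan's birth inputs, births treated as live births, one of the two cited mortality ratios, and an assumed share of 5% to 30%. On these it is about 1 to 6 of 19 deaths, or 2 to 15 of 50, over both arms. Eligibility depends on a post-randomisation event that could differ by arm; whether it would, and in which direction, is not established.

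The point concerns secondary outcomes only. The primary outcomes and the 20-cluster design stand.

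**What to change.** State that the delivery-based rule applies to stillbirth, perinatal and neonatal outcomes only. For maternal mortality, all-cause and cause-specific, count every death of a resident woman during pregnancy, delivery or postpartum that the active surveillance records, whether or not she delivered. Count residence back from the end of pregnancy or from death. Use live births as the denominator, as in the ratios the protocol itself cites.

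The cost is a sentence or two of wording, because surveillance already records maternal deaths without a delivery condition. The sponsor must also state how long after the end of pregnancy a death counts. A denominator of all pregnancies ending by any outcome is not needed. It would cost more, because the surveillance list does not include abortions or miscarriages.

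The change is best made before the one-year interim analysis, whose mortality findings are to be disseminated.

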## 2. Maternal and neonatal health in Pakistan

The health status of women in Pakistan is even poorer in contrast to other neighboring countries in Asia. In recent reports by UNICEF and PDHS, the reported maternal mortality ratio is found to 276 per 100,000 live births. Furthermore, the early mortality or morbidity of a woman is overwhelming and also affects the health of her children. The situation for the under-1 year mortality is 78 and the neonatal mortality is 57. It is estimated that annually 216,000 Pakistani newborns die before they reach their first month of age, which represents 58% of total deaths of children under five. These deaths are more prevalent in rural areas particularly among poor families as compare to urban areas. The maternal mortality in urban areas is 204 compared to 336 per 100,000 live births in Pakistan. Similarly neonatal mortality ratio in urban areas is 48 per 1000 live births compared to 55 per 1000 live births in rural areas. However, NMR in highest wealth quintile is 38 compared to 63 per 1000 live births in lowest wealth quintile.

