## 3. Health care infrastructure in Pakistan

Pakistan has an impressive infrastructure for primary health care with a network of basic health units (BHU) and rural health centers (RHC) (**Figure 2**). While the RHCs and BHUs are staffed by qualified medical and nursing staff, health care at the community level is largely supported by a

large number of trained cadres of lady health workers (LHW) and newly deployed community midwives (CMWs). Although CMWs are trained in the identification of complicated pregnancy and its management, but very few have been deployed so far, and many districts do not have any CMWs. Also the services for basic or comprehensive emergency obstetric or newborn care at the level of BHUs and RHCs are questionable (in terms of quality). Similarly, there is very little emphasis in the current training program of LHWs as well as primary care LHV and physicians on EmONC services. The latter is important as available evidence indicates that despite impressive reduction in infant mortality rates in certain areas such as the northern areas, perinatal mortality still remains distressingly high (AKHSP Northern Areas Annual Report 2000). According to PDHS 2006-07, NMR is high in Punjab (58 per 1000 live births) compared to 30 per 1000 live births in Baluchistan.

There is considerable potential for training of LHWs and CMWs in Pakistan, in order to improve maternal and newborn care. Currently almost 102,000 LHWs are in place, and while they are not directly involved in deliveries, these LHWs are supposed to function in close liaison with BHU and RHC staff in providing antenatal care, contraceptive advice, growth monitoring and immunization services.

A largely ignored cadre of primary care workers in Pakistan is the semi-trained and traditional birth attendants (TBAs). This large group of individuals is responsible for the vast majority of births in rural settings and a large proportion of births even in urban areas (**Figure 3**). The TBA (Dai) has been recognized as an important resource person in the quest for improving reproductive health delivery, both in relation to maternal as well as newborn care, particularly in those areas where no formal health care outreach services are available.

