Historically overlooked by both safe motherhood and child survival policies and programs, newborns continue to lack access to cost-effective lifesaving interventions. The Bellagio Study Group on Child Survival estimates that universal coverage (99%) of 16 proven newborn health interventions could avert up to 72 percent of all newborn deaths. These include interventions such as tetanus toxoid immunization, skilled access to emergency obstetric care, immediate and exclusive breastfeeding, drying and keeping the newborn warm, and if needed, resuscitation, care of low birth weight infants, and treatment of infection. Apart from direct provision of interventions, research has shown that interventions that involve community mobilization and empowerment, and include counseling to mothers on topics related to birth and newborn care preparedness for bringing behavior change can reduce total neonatal deaths by 21% and early neonatal deaths by 24%. On the other hand, improvement of women's access to antenatal, intrapartum and postnatal care with training cadre of community workers, and traditional birth attendant can reduce maternal morbidities by 25% and further improve total neonatal mortalities by 23%. Additional strategies against rising toll of deaths necessitate development in health systems and primary health care to ensure availability of skilled attendance at all levels and access to 24-hour emergency obstetric care. Since many opportunities to optimize birth outcomes occur at the time of birth, therefore it is also important to improve access to skilled birth attendance and emergency obstetric and newborn care that can deliver parenteral administration of drugs, blood transfusion, and surgical interventions when required. Recent reviews and evidence from community based effectiveness studies show that large proportion of these deaths can be saved with the presence of functional referral system.

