### Quantitative approach:

**Cluster randomized control trial** will be used to evaluate the impact of EmONC package for maternal and neonatal health care delivery through community level health care providers. Clusters will be identified and matched on population size, socio-economic status (including structure, electricity, drinking water with HH density), birth/death rates, and number of functional LHWs and CMWs. Cluster Paired randomization will be done to allocate one group (intervention/control) to each cluster and all the LHWs in one union council will be assigned to one group to avoid any sort of contamination.

**Sample Size Calculation:** We are considering Union Council as a cluster. Each Union council serves approximately 15000 - 20000 population and usually contains a Basic health Unit which provides basic facilities of antenatal, natal and post natal care.

- We assume that the average cluster size is 15000 and considering a crude annual birth rate of 20 per 1000 and the estimated average perinatal mortality rate of 60/1000 with a coefficient of variation between clusters of 0.125 and to detect a 25% reduction in the mortality rates, we would require **20 Clusters** in total. Ten clusters per arm to provide the study with a power of 90% over a three-year intervention period.

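### The protocol sizes the trial for perinatal mortality, calls it powered only for neonatal mortality, and makes both primary with no rule for success

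*Protocol*

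**What the plan says.** Three sections of the protocol bear on this.

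- **Quantitative approach, Sample Size Calculation.** The trial is sized on "the estimated average perinatal mortality rate of 60/1000 with a coefficient of variation between clusters of 0.125", with 15,000 people per cluster, 20 births per 1000 per year and three years of intervention, "to detect a 25% reduction in the mortality rates". The result is ten clusters per arm and 90% power. No significance level is given, and no neonatal rate enters the calculation.
- **Study Outcome & Process Indicators.** Two primary outcomes are listed, "All cause neonatal mortality rate" and the perinatal mortality rate. No order is given, and nothing says whether one or both must succeed. The Research Questions section also names both.
- **Statistical analysis of Quantitative Data.** Cause-specific neonatal mortality will be compared between arms, although "the study is only powered for the primary all cause neonatal mortality outcomes".

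**The concern.** The outcome that was sized and the outcome said to be powered are not the same. On the usual definitions, perinatal mortality adds stillbirths to first-week deaths, while neonatal mortality leaves out stillbirths and adds deaths after the first week. The protocol's Justification section puts 75% of neonatal deaths in the first week, so about a quarter of them lie outside the perinatal outcome.

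Taken literally, the word *only* in the power sentence denies power to the one outcome that has a calculation.

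What is at stake is how the trial is read if the two results diverge, for instance if neonatal deaths fall and stillbirths do not. The sample-size section would then support treating perinatal mortality as decisive, the analysis section would support neonatal mortality, and the outcome list would support either. Without a rule, that choice could be made after the data are seen. The protocol also plans an interim analysis of mortality after one year, to be shared with the funder and stakeholders, so the rule is needed before then.

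**Working it through.** **Inputs from the protocol.** Births per cluster: 15,000 × 20/1000 = 300 a year, so m = 900 over three years. Between-cluster coefficient of variation k = 0.125. Relative reduction 25%. Ten clusters per arm.

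**Assumptions.** Two-sided α = 0.05, as none is stated. For neonatal mortality, k, m and the 25% reduction are carried over unchanged. Live births are slightly fewer than all births, with negligible effect.

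**Formula** (Hayes–Bennett, unpaired), clusters per arm:

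c = 1 + (z₀.₉₇₅ + z₀.₉₀)² × V / (p₀ − p₁)², where V = [p₀(1 − p₀) + p₁(1 − p₁)]/m + k²(p₀² + p₁²).

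Power with ten clusters is Φ(√[9(p₀ − p₁)²/V] − 1.96). Leaving out the +1 term puts 10 in place of 9.

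**Step 1: the protocol's own figure** (perinatal, p₀ = 0.060, p₁ = 0.045).

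- V = 0.099375/900 + 0.015625 × 0.005625 = 0.00011042 + 0.00008789 = 0.00019831
- (p₀ − p₁)² = 0.000225
- c = 1 + 10.507 × 0.00019831/0.000225 = 1 + 9.26 = 10.26
- Power at ten clusters: Φ(3.196 − 1.96) = 89.2%. Without the +1 term, c = 9.26 and power is Φ(3.368 − 1.96) = 92.0%.

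Ten clusters per arm at 90% therefore reproduces, and the outcome it reproduces for is perinatal mortality.

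**Step 2: the same design for neonatal mortality.** The background sections give 48 urban and 55 rural, 57 nationally, and for the province "NMR is high in Punjab (58 per 1000 live births". At 55 per 1000, p₁ = 0.04125, V = 0.00010169 + 0.00007385 = 0.00017555 (after rounding) and (p₀ − p₁)² = 0.00018906. Power is Φ(3.113 − 1.96) = 87.6%.

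| Outcome and control rate per 1000 | c with +1 | Power, with +1 | Power, without +1 |
|---|---|---|---|
| Perinatal 60 | 10.26 | 89.2% | 92.0% |
| Neonatal 58 | 10.45 | 88.6% | 91.5% |
| Neonatal 57 | 10.55 | 88.2% | 91.3% |
| Neonatal 55 | 10.76 | 87.6% | 90.7% |
| Neonatal 48 | 11.62 | 84.7% | 88.2% |
| Neonatal 40 (assumed) | 12.99 | 80.2% | 84.2% |

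At 55 to 58 per 1000 the change of outcome costs about 0.5 to 2 points. At the urban 48 it costs about 4 to 5.

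**Step 3: no success rule.** Suppose each primary were tested at two-sided 5% and either could be claimed. With no true effect and bivariate normal test statistics, the chance of at least one false positive is 9.1% at correlation 0.5, 8.3% at 0.7 and 7.8% at 0.8. Independence gives the ceiling, 1 − 0.95² = 9.75%. The correlation is an assumption. A rough guide is the overlap in deaths: 75% of 55 is about 41 shared deaths per 1000, and 41/√(60 × 55) = 0.71.

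**The case against.** The strongest defence is context. The power sentence sits in a remark on cause-specific neonatal mortality. Its purpose is to warn that cause-specific results are underpowered compared with all-cause results, not to choose between neonatal and perinatal mortality, and the plural in it may be loose shorthand for the primaries. That explains how the sentence arose, but all-cause neonatal mortality was never sized, so it remains inaccurate.

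A second defence is that multiplicity rules often sit in a statistical analysis plan, which is not available here. That stands for the choice of method. It does not excuse the protocol's conflicting statements about what the trial was designed to show.

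A reader might draw three stronger conclusions that the document does not support.

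- **That the 90% is attached to the wrong outcome.** It appears only in the sample-size section, for perinatal mortality, a listed primary outcome, and it reproduces there. The analysis section quotes no power figure.
- **That neonatal power falls well short.** Allowing for pairing (+2 in place of +1, no gain from matching) gives 83.5% to 84.7% at 55 to 58 per 1000, but perinatal power then also falls, to 85.4%. The background says that community mobilisation "can reduce total neonatal deaths by 21% and early neonatal deaths by 24"%, and cites 23% for training of community workers. Reductions of 21% to 23% in the paired calculation give 68% to 76% for neonatal mortality at 55, but 70% to 79% for perinatal mortality at 60. The drop comes from pairing and the smaller effect, not the outcome mismatch. The same background section also cites a 25–30% reduction in perinatal and neonatal mortality in an earlier Pakistani trial, which supports the planned 25%.
- **That the plan allows success on either outcome at 5%.** It neither allows nor forbids this.

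**Conclusion.** The inconsistency is real and should be fixed. The protocol gives incompatible accounts of which primary outcome carries the power, and names two primaries without a success rule. The sample size itself is not in doubt for perinatal mortality.

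The effect on power is small: under 2 points at neonatal rates of 55 to 58 per 1000 and 4 to 5 at 48. It becomes material only if the true neonatal rate is well below the protocol's figures. This rests on two-sided 5% and on carrying the perinatal k and 25% reduction over to neonatal mortality.

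The more consequential part is the missing rule. The error rate of roughly 8% to 9% is conditional on an either-or claim and a correlation of 0.5 to 0.8. It measures what the silence leaves open, not a property of a stated test.

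**What to change.** 1. In the analysis section, replace the power clause with a statement that the study was sized for perinatal mortality. Beside it give the neonatal power on the same inputs: about 88% to 89% at 55 to 58 per 1000 and about 85% at 48 (unpaired, with the +1 term), listing the assumed α, k and reduction. Keep the caution about cause-specific mortality.
2. In the sample-size section, state the significance level and its sidedness.
3. In the outcomes section, set one success rule before any outcome comparison, including the one-year interim. A fixed sequence would do: perinatal mortality at 5%, then neonatal mortality at 5% only if the first is significant. It needs no extra clusters and costs the perinatal test no alpha. Its small downside is that a neonatal claim becomes conditional on the perinatal result.

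The sequence is one choice among several, since the research question names both outcomes. Requiring both to succeed needs no alpha adjustment but lowers the chance of overall success. Splitting alpha equally (2.5% each) keeps both claims independent, at the price of power of about 83% for perinatal and 81% to 82% for neonatal mortality at 55 to 58 per 1000 (unpaired, with the +1 term).

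Under the fixed sequence the whole change is wording in three sections.
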